## Abstract

**Introduction:**

The incidence of lumbar disc degeneration disease has increased in recent years. Lumbar interbody fusion using two unilateral pedicle screws and a translaminar facet screw fixation has advantages of minimal invasiveness and lower costs compared with the traditional methods. Moreover, a method guided by a three-dimensional (3D) navigation template may help us improve the surgical accuracy and the success rate. This is the first randomised study using a 3D navigation template to guide a unilateral lumbar pedicle screw with contralateral translaminar facet screw fixation.

**Methods and analysis:**

Patients who meet the criteria of the surgery will be randomly divided into experimental groups and control groups by a computer-generated randomisation schedule. We will preoperatively design an individual 3D navigation template using CATIA software and MeditoolCreate. The following primary outcomes will be collected: screw angles compared with the optimal screw trajectories in 3D digital images, length of the wound incision, operative time, intraoperative blood loss and complications. The following secondary outcomes will be collected: visual analogue scale (VAS) for back pain, VAS for leg pain and the Oswestry Disability Index. These parameters will be evaluated on day 1 and then 3, 6, 12 and 24 months postoperatively.

**Ethics and dissemination:**

The study has been reviewed and approved by the institutional ethics review board of the Second Affiliated Hospital and Yuying Children’s Hospital of Wenzhou Medical University. The results will be presented at scientific communities and peer-reviewed journals.

**Trial registration number:**

ChiCTR-IDR-17010466

Strengths and limitations of this studyThis is the first multicentre randomised controlled trial to compare a three-dimensional (3D) navigation template for guiding a unilateral lumbar pedicle screw with contralateral translaminar facet screw fixation versus traditional multiple X-ray fluoroscopy.We will first use Mimics and CATIA software to design the 3D navigation template of a unilateral lumbar pedicle screw with contralateral translaminar facet screw fixation.The clinical data will be collected prospectively at least 24 months after the operation.Because this is a multicentre randomised controlled trial, the surgeons’ experiments at different research sites may influence the outcomes.

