## Methods and analysis

The study has been reviewed and approved by the institutional ethics review board of the Second Affiliated Hospital and Yuying Children’s Hospital of Wenzhou Medical University. All of the participants will sign their informed consent. The protocol has been registered in the Chinese Clinical Trial Registry (ChiCTR), assigned to be the representative registry of China to join the WHO ICTRP in 2007, with protocol number ChiCTR-IDR-17010466. The 2013 SPIRIT checklist (see online supplementary table 1) was used to check our reports.^19 20^

10.1136/bmjopen-2017-016328.supp1Supplementary file 1

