### Participants

This study is a parallel group RCT conducted at the Orthopaedic Hospital, Second Affiliated Hospital and Yuying Children’s Hospital of Wenzhou Medical University.

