### Randomisation and blinding

Patients will be randomly divided into an experimental group and a control group using a computer-generated randomisation schedule. The random sequence will be stored in a sealed opaque envelope to ensure that the patients, personnel and the outcome assessor will be blinded to the group allocation. Until the last questionnaires have been completed, the participant’s allocated intervention will be revealed by the study secretary. If a patient's condition deteriorates, the blinding experiment will be terminated, and the patient’s safety will be given the highest priority (figure 1).

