### Study procedure

A retrospective review of all patients will be conducted by examining their medical records before the operation. The involved segments were identified via a C-arm machine and then marked on the patient’s skin. The patients’ CT images with a thickness less than 1 mm will be exported from the Star PACS image system of the hospital and imported into the Mimics 16.0 to construct 3D images, in which we adjust the threshold depending on the bone density. We regard the two adjacent segments as a functional segmental unit (FSU), such as L2-3, L3-4, L4-5 or L5-S1.

Then, the individual 3D navigation templates will be designed and printed using CATIA software and MeditoolCreate. The detailed steps are as follows: the FSU digital data in the Mimics 16.0 will be saved in STL format and imported into CATIA software. We will establish the optimal screw trajectory, which includes two vertebral pedicle screws trajectories and one contralateral translaminar facet screw trajectory. We will measure three angles of the translaminar facet screw trajectory: α, β and γ; α is the angle between the screw trajectory and the vertical line in the anteroposterior view; β is the angle between the screw trajectory and the upper endplate of the lower vertebra in the lateral view; γ is the angle between the screw trajectory and the midline of the lumbar vertebra in the top view (figure 2). The pedicle screw trajectories will be designed according to method of Roy-Camille.^22^ We will measure two angles, δ and ε, which is the angle between the ideal screw trajectory and the midline of the lumbar vertebra in the top view, respectively (figure 2).

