### Statistical analysis

All data will be analysed using SPSS V.19.0 software. The differences in wound incision length, operative time, intraoperative blood loss and angles between the two groups will be analysed using a two independent-sample t-test with an α of 0.05. VAS and ODI scores at preoperation, postoperation, 3 months postoperatively, 6 months postoperatively and 12 months postoperatively will be analysed using a repeated-measures analysis of variance. The times of X-ray exposure and frequency of screw penetration out of the cortex will be compared using the χ^2^ test.

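### The article calls the trial multicentre but names one institution, and the tests it fixes leave out the surgeon and site influence it admits

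*Protocol article*

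**What the plan says.** The Strengths and limitations box, printed after the trial registration number, claims the first multicentre randomised comparison of the template with fluoroscopy. It then lists a limitation that opens "Because this is a multicentre randomised controlled trial" and goes on to say that the experiments of surgeons at the various sites could affect the results. I take the word experiments there to mean experience.

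The Participants section describes the setting differently: "This study is a parallel group RCT conducted at the Orthopaedic Hospital, Second Affiliated Hospital and Yuying Children’s Hospital of Wenzhou Medical University". The abstract, the opening of Methods and analysis, and the Ethics and dissemination section each cite one board, the "institutional ethics review board of the Second Affiliated Hospital and Yuying Children’s Hospital of Wenzhou Medical University". Under Study procedure, CT images are "exported from the Star PACS image system of the hospital", in the singular.

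On allocation, Randomisation and blinding says: "Patients will be randomly divided into an experimental group and a control group using a computer-generated randomisation schedule". It does not say whether that schedule is stratified.

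In Statistical analysis, incision length, operative time, blood loss and the screw angles "will be analysed using a two independent-sample t-test with an α of 0.05". X-ray exposure and cortical penetration are compared by chi-square test, and VAS and ODI by repeated-measures analysis of variance. No site or surgeon term is mentioned for any of them. The only step that bears on operator differences is in Monitoring, where surgeons, in the plural, are to be trained beforehand.

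**The concern.** Two statements in the same article disagree on how many centres take part. Condensing a longer protocol does not explain that. If the trial is single-centre, the novelty claim and the stated limitation are both wrong, and readers will credit the results with wider applicability than they have. If it is multicentre, the sites are not named.

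The article also names a source of outcome variation and then fixes tests that cannot account for it. Incision length, operative time, blood loss, X-ray exposure, screw angles and screw position are all listed as primary outcomes, and all could plausibly vary with the operator. An unadjusted test leaves variation between sites or surgeons in the error term. At stake are precision and clarity about what the trial can claim.

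**Working it through.** **Step 1: the number of centres.**

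| Place in the article | What it implies |
|---|---|
| Strengths and limitations box, first item | Multicentre |
| Strengths and limitations box, last item | Multicentre, with several research sites |
| Participants | One named institution |
| Abstract; Methods and analysis; Ethics and dissemination | One ethics board, same institutional name |
| Study procedure | One hospital's imaging system |
| Anywhere else | No second site named |

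The commas and the conjunction in the Participants sentence could suggest a list of hospitals. But the ethics statements use the Second Affiliated Hospital and Yuying Children's Hospital as the name of one institution with one institutional board. The natural reading is one institution, which does not fit the box.

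**Step 2: what the fixed tests can carry.** A two-sample t-test and an ordinary chi-square test have no place for a further factor. A repeated-measures analysis of variance can take a between-subject factor, but the article mentions none for site or surgeon.

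**Step 3: the plan's own figure.** The article gives no figure for site or surgeon variation. Its one calculated figure is the sample size of 132, from 84.6% versus 95%, power 0.8 and α 0.05. With mean proportion 0.898, the two-sided pooled formula gives

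n = [1.960·√(2·0.898·0.102) + 0.842·√(0.846·0.154 + 0.95·0.05)]² / 0.104² = (0.839 + 0.355)² / 0.010816 ≈ 132 per arm.

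So 132 reproduces, as a per-arm figure, from a plain two-proportion calculation with no site term. It does not affect the present point.

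**Step 4: the size of the effect for a continuous outcome.** Let R² be the share of outcome variance due to site or surgeon. The documents do not give it, so the values below are assumed. Each site or surgeon is assumed to treat patients in both arms, and the few degrees of freedom spent on the factor are ignored.

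- Gain in equivalent sample size from adjusting: 1/(1−R²) − 1.
- Adjusted power, for an effect with nominal 80% power: Φ[(1.960 + 0.842)/√(1−R²) − 1.960].
- Unadjusted t-test when allocation is balanced within site: type I error 2[1 − Φ(1.960/√(1−R²))]; power Φ[0.842/√(1−R²)].

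| Assumed R² | Gain in sample size | Power, adjusted | Type I error, unadjusted, balanced within site | Power, unadjusted, balanced within site |
|---|---|---|---|---|
| 0.01 | 1.0% | 80.4% | 4.9% | 80.1% |
| 0.05 | 5.3% | 82.0% | 4.4% | 80.6% |
| 0.10 | 11.1% | 84.0% | 3.9% | 81.3% |
| 0.20 | 25.0% | 87.9% | 2.8% | 82.7% |

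Example for R² = 0.20: √0.8 = 0.894. Then 2.802/0.894 − 1.960 = 1.172, which gives 87.9% power, and 1.960/0.894 = 2.191, which gives a type I error of 2.8%.

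The formulas are for linear models of continuous outcomes. They do not carry over directly to screw penetration or to the proportions behind the sample size.

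**The case against.** The strongest reply is that only the wording conflict is certain. One ethics board does not by itself prove a single centre. Details of stratification and blocking are commonly left to a full protocol, and covariate adjustment to an analysis plan, and neither document is shown. The size of any gain is assumed, and at an R² of 0.01 to 0.05 it is small. Surgeon training may reduce operator differences.

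Much of this stands. In particular, three stronger readings are tempting but not supported:

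- *Allocation is unstratified.* The article is silent, and silence in a condensed article is not evidence of simple randomisation.
- *A chance imbalance of surgeons between arms biases the results or inflates false positives.* Under randomisation such imbalance adds variance to the estimate. It does not bias the estimator, and the unadjusted standard error already allows for it. With balance within site, the unadjusted test errs on the conservative side.
- *Surgeon is known to drive these outcomes strongly.* The article says only that it may have an influence, and it reports no variance share.

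The reply does not dispose of two things. Two statements about the setting in the same article cannot both be right as written. And the t-tests and chi-square tests are stated methods, so this part of the point does not rest on an omission. Training is neither a randomisation nor an analysis measure.

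**Conclusion.** The article contradicts itself on whether the trial is multicentre, and the contradiction should be resolved because it bears on the claimed strength, the stated limitation and how far the results can be generalised. The text points to one institution but does not settle the matter.

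The tests fixed for the operative and accuracy outcomes remain valid, but they ignore an influence that the article itself names. The cost is precision: for continuous outcomes, the equivalent of about 1% of the sample at R² = 0.01, 5% at 0.05 and 25% at 0.2. All three values are assumed, and the true value may be anywhere in that range or outside it. If allocation is balanced within site, the unadjusted t-test also runs below its nominal 5%, at 2.8% to 4.9% over the same range. The analysis part applies only if more than one site or surgeon takes part. The plural in the Monitoring section suggests this but does not establish it.

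**What to change.** 1. Reconcile the Strengths and limitations box with the Participants section. Either name the participating sites, or remove the multicentre claim and the limitation that depends on it.
2. If more than one site or surgeon takes part, include site (or operating surgeon, if single-centre) in the analysis:
   - a linear model with arm and that factor in place of the t-test;
   - a Cochran-Mantel-Haenszel or logistic analysis in place of the chi-square test for screw penetration;
   - a between-subject factor in the repeated-measures analysis of variance for VAS and ODI.
3. State whether allocation is stratified by site. If it is, the analysis should reflect it.

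The cost is a wording change, one extra model term and slightly more analysis work. No extra patients are needed, and the change can be made after recruitment has started, provided it is fixed before outcome data are examined by arm. If one surgeon at one centre performs every operation, only item 1 and the statement on allocation remain.

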## Introduction

With the ageing of society, the incidence of lumbar disc degeneration disease is increasing,^1 2^ which is a major socioeconomic burden.^3–5^ If conservative treatment of lumbar degenerative disease is ineffective, surgical intervention is recommended for these patients.^6–9^ Compared with the pedicle screw fixation on both sides, which has gained popularity among general surgeons because of easiness, the lumbar interbody fusion, which uses two unilateral pedicle screws and a translaminar facet screw fixation, can reduce tissue trauma and the length of the wound incision, as well as promote recovery.^10–12^

The translaminar screw is a long screw that goes through the spinous process and zygapophyseal joints and ends in a lower vertebral facet to fix the other side of the joint.^13^ The biomechanical properties of the translaminar screw are the same as pedicle screws in vitro biomechanical experiments.^14 15^ Park *et al*^16^ reported that the visual analogue scale (VAS) and Oswestry Disability Index (ODI) scores of the patient were significantly improved after minimally invasive surgery of anterior lumbar interbody fusion combined with the translaminar screw. Liu *et al*^11^ reported a recovery rate of 93.5% through minimally invasive surgery of transforaminal lumbar interbody fusion combined with the translaminar screw.

However, there is higher risk of nerve and vascular injury when the angle deviation of the translaminar screw or screw entry point is incorrect.^17^ To achieve an optimal screw trajectory, many surgeons choose multiple X-ray images as a guide to locate the entrance point and adjust the angle, which will expose both patients and surgeons to considerable radiation.^11 12 18^ The technique of three-dimensional (3D) reconstruction and a 3D rapid printed navigation template, which extracts the posterior surface features of the lumbar vertebrae, may help determine the optimal trajectory of translaminar facet screw fixation.

To the best of our knowledge, there are no randomised controlled studies of a 3D navigation template versus traditional multiple X-ray fluoroscopy for guiding a unilateral lumbar pedicle screw with contralateral translaminar facet screw fixation. In this study, we will conduct a randomised controlled trial (RCT) to compare 3D navigation template for guiding a unilateral lumbar pedicle screw with contralateral translaminar facet screw fixation versus traditional multiple X-ray fluoroscopy.

## Methods and analysis

The study has been reviewed and approved by the institutional ethics review board of the Second Affiliated Hospital and Yuying Children’s Hospital of Wenzhou Medical University. All of the participants will sign their informed consent. The protocol has been registered in the Chinese Clinical Trial Registry (ChiCTR), assigned to be the representative registry of China to join the WHO ICTRP in 2007, with protocol number ChiCTR-IDR-17010466. The 2013 SPIRIT checklist (see online supplementary table 1) was used to check our reports.^19 20^

10.1136/bmjopen-2017-016328.supp1Supplementary file 1

### Participants

This study is a parallel group RCT conducted at the Orthopaedic Hospital, Second Affiliated Hospital and Yuying Children’s Hospital of Wenzhou Medical University.

#### Inclusion criteria

Adult patients older than 18 years;Lower back pain that is chronic or combined with neurological symptoms of the lower extremities;Single-segment lower lumbar vertebral disease (including lumbar spinal canal stenosis, foraminal stenosis, segmental instability, lumbar disc herniation and painful disc degeneration (back disc)); andInefficacy after strict conservative treatment for more than 6 months.

#### Exclusion criteria

Serious deformity of the lumbar vertebrae;Dysplasia of the lumbar pedicle or vertebral lamina;Obvious osteoporosis of the lumbar vertebrae;Metabolic bone diseases such as osteomalacia or Paget’s disease;Spondylolisthesis grade >2 (Meyerding);Cauda equina injury or severe radiculopathy;Postinflammatory instability of the vertebral spine;Body mass index >30;Immunological diseases or metabolic syndrome;Therapy with systematic corticosteroids or immunosuppressants; andCurrent use of Coumadin (warfarin) or heparin therapy for more than 6 months at the time of the operation.

#### Sample size calculation

We performed a power analysis to assess the required sample size to show safety with a power (1−b) of 0.8 and α of 0.05. Based on the pre-experiment and related literature,^21^ the proportion of the control group was set to 84.6%, and the proportion of intervention group was set to 95%. We performed a two independent proportions power analysis on PASS (Power Analysis and Sample Size), and the result was 132.

### Randomisation and blinding

Patients will be randomly divided into an experimental group and a control group using a computer-generated randomisation schedule. The random sequence will be stored in a sealed opaque envelope to ensure that the patients, personnel and the outcome assessor will be blinded to the group allocation. Until the last questionnaires have been completed, the participant’s allocated intervention will be revealed by the study secretary. If a patient's condition deteriorates, the blinding experiment will be terminated, and the patient’s safety will be given the highest priority (figure 1).

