**Figure 5 F5:**
[figure not shown]
One example of the experiment on conducted 3D printed lumbar model before clinical application to make sure the accurate screw trajectory.

The 3D navigation template will be sterilised and used to guide the screw in further operations on the patients. In experimental group, the dissection of the paraspinal tissue will performed at one side to expose the part of spinous process, laminar and facet joint; the 3D navigation template will be attached to the surface of the above bony construction. Then, the Kirschner wire (K-wire) will be inserted inside the 3D navigation template, and a trajectory for the screw will be fashioned with a cannulated drill; screws will be subsequently introduced. In the control group, multiple X-ray fluoroscopy will be used, and the screw trajectory will be adjusted by intraoperative X-ray fluoroscopy.

After the operation, CT scans of the patients in both groups will be obtained, and the α1, β1, γ1, δ1 and ε1 angles will be measured corresponding to the angles of the optimal screw trajectory in 3D images. The placement and position of the screws will be divided into three types (type I, the screw does not penetrate out of the cortex; type II, the screw partially penetrates out of the cortex, but by less than 2 mm; and type III, the screw penetrates out of the cortex by more than 2 mm).

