### Outcome measure

#### Primary outcomes (table 1)

**Table 1 T1:** The data need to collect through the research

	Baseline	Perioperation	Postoperation				
Assessment	−1 day	Day 0	Day 1	3 months	6 months	12 months	24 months
Eligibility criteria	×						
Recruitment	×						
Informed consent	×						
Randomisation	×						
Baseline demographics	×						
Medical history	×						
X-ray exposure		×					
Wound incision length		×					
Operative time		×					
Blood loss		×					
Complications		×	×	×	×	×	×
Screw angles							
α1			×				
β1			×				
γ1			×				
δ1			×				
ε1			×				
The position of the screws			×				
VAS of back pain	×		×	×	×	×	×
VAS of leg pain	×		×	×	×	×	×
ODI	×		×	×	×	×	×

ODI, Oswestry Disability Index; VAS, visual analogue scale.

Screw angles compared with the optimal screw trajectories in the 3D digital images and the position of the screws.Wound incision length, operative time, intraoperative blood loss, times of X-ray exposure and complications.

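### The protocol claims blinding of personnel, which is impossible for the operating team, and its sentence on revealing allocation is worded backwards

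*Protocol article*

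**What the plan says.** The Randomisation and blinding section of the protocol article gives one mechanism: "The random sequence will be stored in a sealed opaque envelope". Its stated purpose is "to ensure that the patients, personnel and the outcome assessor will be blinded to the group allocation". The next sentence is the only routine rule on disclosure: "Until the last questionnaires have been completed, the participant’s allocated intervention will be revealed by the study secretary". The section then provides for ending the blinding if a patient deteriorates.

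The Study procedure section (the text after the legend of Figure 5) describes what is done in each arm. In the experimental arm, "the 3D navigation template will be attached to the surface of the above bony construction", and a K-wire is passed through it. For the comparator: "In the control group, multiple X-ray fluoroscopy will be used, and the screw trajectory will be adjusted by intraoperative X-ray fluoroscopy".

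The Primary outcomes section lists the screw angles and screw position, and then "Wound incision length, operative time, intraoperative blood loss, times of X-ray exposure and complications". The secondary outcomes are VAS for back pain, VAS for leg pain and ODI, collected up to 24 months.

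**The concern.** Two statements in the blinding section cannot stand as written.

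The first is the claim that personnel are blinded. Nothing in the section excludes the surgeon and theatre staff from that word, yet they carry out the allocated method. Several primary outcomes arise while they do so. A reader who accepts the claim would give those outcomes the credit of a blinded comparison, which they do not have. Knowledge of the arm can affect how an operation is conducted and how a quantity such as blood loss is estimated, even without intent.

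The second is the rule on disclosure. VAS and ODI are reported by patients, so they depend on patients staying unaware of their arm throughout follow-up. The rule that should secure this says the opposite if followed to the letter.

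**Working it through.** The plan gives no figure on this point, so the check sets the statements side by side and counts the outcomes affected.

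**1. Can personnel be blinded?** One arm has a printed guide placed on the exposed bone; the other relies on repeated imaging to adjust the trajectory. Whoever performs or assists at the operation sees which is used. The claim is therefore false for the operating team. It may be true for people outside theatre.

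**2. What can the envelope do?** It hides the sequence until a patient is assigned, which is allocation concealment. Once the arm is known in theatre, the envelope has no further effect. It therefore cannot by itself deliver what the section says it ensures.

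**3. Which outcomes are touched?** From the Primary outcomes list and Table 1:

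| Primary items | Number | When recorded (Table 1) | Where it arises |
|---|---|---|---|
| Screw angles α1, β1, γ1, δ1, ε1 | 5 | Day 1 | postoperative CT |
| Screw position | 1 | Day 1 | postoperative CT |
| Incision length, operating time, blood loss, X-ray exposure | 4 | Day 0 only | theatre |
| Complications | 1 | Day 0 and every later visit | theatre and follow-up |

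Total: 5 + 1 + 4 + 1 = 11. Four of the 11 arise only in theatre, and the intraoperative part of a fifth does too. If the five angles are counted as one item, the total is 1 + 1 + 4 + 1 = 7, and the same four are four of seven. The six CT items can be read by someone who was not in theatre.

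**4. What does the disclosure sentence say?** It has two parts: "Until the last questionnaires have been completed", then that the "allocated intervention will be revealed by the study secretary". Joined as printed, disclosure is allowed up to the last questionnaire. The sentence before it says that patients and the assessor are blinded. The sentence after it describes an exception in which blinding ends, which makes sense only if blinding otherwise continues. Both neighbours fit 'not until' and neither fits the printed wording.

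**The case against.** The strongest reply is that little is lost. Patients, a CT reader and a questionnaire collector can all be blinded in this design. Incision length, operating time and exposure counts are measured quantities rather than ratings. The disclosure sentence is evidently a language slip, and a journal article may leave the details of blinding to the full protocol.

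Much of this stands, and it rules out three stronger readings that a reader might infer:

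- *That the outcomes have no protection at all.* Nothing in the document prevents blinding of the patient, a separate CT reader or a separate collector of VAS and ODI. The failure is confined to the operating team and to the envelope as the stated means.
- *That the trial plans to disclose allocation during follow-up.* The surrounding sentences point to a slip. The document gives no evidence that VAS or ODI will in fact be exposed.
- *That the unblinded team records the theatre outcomes.* The Monitoring section mentions surgeons and data collectors separately. It does not say who records each operative variable or whether the collectors know the arm.

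The argument from condensation does not remove the point. The complaint is not that detail is absent: the article makes a positive claim that its own description of the operations contradicts, and it prints a rule in reverse. Measured quantities are also not immune, because the team that knows the arm influences how they come about, whoever writes them down.

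**Conclusion.** The point holds in limited form. As written, blinding of personnel is untrue for the operating team, and the sealed envelope secures concealment only before assignment. Four primary outcomes (four of 11, or four of seven if the angles count as one), together with intraoperative complications, cannot be regarded as protected by blinding of personnel. The disclosure rule is reversed and contradicts its own section; it is most plausibly a slip, but it is an operating instruction and must be right.

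The direction and size of any bias cannot be derived from the document. The conclusion assumes that the word personnel includes those in theatre, which the text does not exclude. The randomised comparison itself is not invalidated. What changes is how the theatre outcomes may be described and interpreted.

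**What to change.** In the Randomisation and blinding section:

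1. Describe the envelope as the means of concealing the sequence before assignment.
2. State that the surgeon and theatre staff are not blinded, and that the patient, the reader of the postoperative CT and the collector of VAS and ODI are.
3. Replace the disclosure sentence with a rule such as: allocation will not be revealed until the last (24-month) questionnaire has been completed.

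In the outcome section and the eventual report, label incision length, operating time, blood loss, X-ray exposure and intraoperative complications as unblinded.

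The cost is mostly a change of wording, provided that the CT reader and the questionnaire collector are people who were not in theatre. The document does not say whether they are. The drawback is that the blinding claim becomes less favourable.

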#### Secondary outcomes (table 1)

VAS for back pain;VAS for leg pain; andODI.

The data will be collected preoperatively; on day 1 postoperatively; and then at 3, 6, 12 and 24 months postoperatively.

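### Blinding ends whenever a patient deteriorates, with no threshold and no need-to-know condition, so patients who worsen may be unmasked before their later VAS, ODI and complication assessments

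*Protocol article*

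**What the plan says.** The Randomisation and blinding section of the protocol article makes three relevant statements.

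- Who is masked: "the patients, personnel and the outcome assessor will be blinded to the group allocation".
- When an allocation is normally disclosed: "Until the last questionnaires have been completed, the participant’s allocated intervention will be revealed by the study secretary". The English is awkward, but the evident intent is that masking lasts through the final questionnaire.
- When masking ends early: "If a patient's condition deteriorates, the blinding experiment will be terminated, and the patient’s safety will be given the highest priority".

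The Study procedure section describes what happens in theatre. In the experimental arm, "the 3D navigation template will be attached to the surface of the above bony construction". For the other arm: "In the control group, multiple X-ray fluoroscopy will be used, and the screw trajectory will be adjusted by intraoperative X-ray fluoroscopy".

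On the timing of VAS and ODI, the Secondary outcomes section says: "The data will be collected preoperatively; on day 1 postoperatively; and then at 3, 6, 12 and 24 months postoperatively". Table 1 gives the same schedule. It also follows complications, which are listed among the primary outcomes, from day 0 to 24 months.

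**The concern.** Provision to break the code for safety is normal, usually where knowing the allocation would change what is done for the patient. Here the trigger is deterioration itself, whether or not the allocation matters to care, and the action is worded as automatic. In a population operated on for back and leg symptoms, worsening pain or disability is one ordinary meaning of deterioration. VAS and ODI measure pain and disability, so the trigger is related to the outcomes that masking is meant to protect.

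If the rule is followed as written, a patient who worsens may report later scores knowing which technique was used, and an assessor may judge later complications with the same knowledge. Either could shift the comparison between arms. The shift would come from patients doing poorly, who carry much of the information on pain, disability and complications.

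**Working it through.** No figure in the article bears on this point. The only computed figure, the sample size of 132, does not enter. The check is therefore a comparison of the texts.

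**1. Trigger.** The operative words are "condition deteriorates, the blinding experiment will be terminated". They contain no definition of deterioration, no severity level and no condition that the allocation be needed for care. The stated purpose is safety ("safety will be given the highest priority"), but the action does not depend on whether disclosure would serve it.

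**2. Unit.** The sentence begins and ends with a single patient, and the sentence before it concerns one participant's allocation. The natural reading is that the code is broken for that patient.

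**3. Outcomes still to be collected (Table 1 and Secondary outcomes).**

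| Outcome | Recorded | Exposed to later unmasking |
|---|---|---|
| Incision length, operative time, blood loss, X-ray exposure | Day 0 | Largely not |
| Screw angles, screw position | Day 1 | Largely not |
| Complications | Day 0, day 1, then 3, 6, 12, 24 months | Yes, after day 1 |
| VAS back, VAS leg, ODI | Baseline, day 1, then 3, 6, 12, 24 months | Yes, after day 1 |

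There are five postoperative VAS and ODI assessments. If a patient is unmasked between day 1 and 3 months, four remain. Between 3 and 6 months, three remain; between 6 and 12 months, two; between 12 and 24 months, one.

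**4. Form of the bias.** At a given visit, let f be the fraction of an arm's patients already unmasked, and d the average change in their recorded score caused by knowing the allocation. The bias in the difference between arm means is

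f(template) × d(template) − f(fluoroscopy) × d(fluoroscopy).

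If deterioration differs by arm, the two values of f differ. Even if f is the same in both arms, the bias is f × [d(template) − d(fluoroscopy)], which is not zero when knowing that one technique was used affects ratings differently from knowing that the other was. The article gives neither f nor d, so no value can be calculated and the direction is unknown.

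**5. What disclosure adds.** The Study procedure section has the surgeon either fit a printed template to bone or adjust the trajectory under fluoroscopy. The operating surgeon therefore knows the arm before any deterioration can occur. For a decision taken by that surgeon, ending the blind supplies nothing new. It could inform other treating staff, but the rule is not limited to cases where they need it.

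**6. Consistency.** Step 5 also contradicts the statement that personnel are blinded, unless that word is meant to exclude the operating team. The article does not say so.

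**The case against.** The strongest case against the point is that it makes a defect out of loose English. Breaking the blind for safety is standard, and a condensed article may leave the operational procedure, such as who is told and how it is logged, to the full protocol. The sentence also refers to Figure 1, which is not shown. VAS and ODI are secondary, and most primary outcomes are fixed by day 1.

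Much of this stands. Missing operational detail is not a finding here, and the reach is limited as described. What remains is the rule that the article does state, with a trigger tied to the patient's course and no need-to-know limit. Further detail elsewhere could add to that rule, but the published wording would still need correcting.

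A reader might also infer three stronger things, which the documents do not support.

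- **That one deterioration ends blinding for the whole trial.** The phrase taken alone can be read so, but the surrounding wording concerns an individual patient.
- **That exactly the patients with the worst outcomes are unmasked.** Deterioration is undefined and is not tied to VAS, ODI or complications. It could mean an acute medical event. Nor does the text say who would be told. The supportable statement is that patients who worsen are preferentially unmasked.
- **That disclosure adds no safety.** Over 24 months a patient may be seen by staff who were not in theatre and do not know the arm. The gain is doubtful, but its absence is not shown.

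**Conclusion.** The concern holds in limited form. The article fixes an automatic, outcome-related trigger for ending masking, with no threshold and no condition that care requires the allocation. On the per-patient reading, this opens a bias path for VAS back, VAS leg, ODI and complications at the 3, 6, 12 and 24 month assessments. The imbalance may be greater if deterioration differs by arm. Outcomes recorded on day 0 or day 1, apart from the later follow-up of complications, are largely unaffected.

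The size cannot be computed from the document. The conclusion assumes that the rule is applied as worded, that deterioration is at least partly related to pain, disability or complications, and that ending the blind means the patient, the assessor or both learn the allocation. Separately, the claim that personnel are blinded cannot be squared with the Study procedure section as far as the operating surgeon is concerned. The point is worth correcting, but it does not undermine the perioperative and screw-placement comparisons.

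**What to change.** Replace the sentence in Randomisation and blinding with wording to this effect:

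- Only the affected patient's code may be broken, and only when the investigators judge that the allocation is needed for that patient's care.
- The outcome assessor and all other patients stay masked.
- Where feasible, VAS and ODI are recorded before disclosure.
- The patient stays in all scheduled follow-up. This matters because the Monitoring section replaces the data of patients lost to follow-up with the average. The article does not say that an unmasked patient leaves, but if one did, a poor score could be replaced by an average one.
- Each break is logged with date, reason and arm, and the breaks are reported with the results.

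In the same revision, reconcile Randomisation and blinding with Study procedure by naming who is masked and acknowledging that the operating surgeon is not.

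How a deteriorating patient is cared for stays with the investigators, and nothing here bears on it. The cost is a few sentences and a log.
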